#### Intervention fidelity and data quality assurance.

A standardized protocol governs the delivery of the pneumoperitoneum pressure. Laparoscopic cholecystectomy will be performed according to routine clinical care practices. A comprehensive fidelity monitoring plan will be implemented to ensure consistent and reliable delivery of both the intervention and control conditions. This plan addresses key fidelity domains, including adherence, delivery quality, and data accuracy. After each operation, the surgeon will complete a fidelity log documenting operation time, protocol deviations or intraoperative incident. Data quality will be ensured through double data entry and verification processes. This structured fidelity and quality assurance approach is designed to uphold the trial’s internal validity and support accurate interpretation of the intervention’s effects.

### Study endpoints

#### Primary endpoint.

Postoperative pain at 6th postoperative hour (H6): defined as abdominal and/or interscapular pain measured by a Visual Analog Scale (VAS) as following, from 0 to 10: 0 no pain, 5 moderate pain, 10 worst possible pain.

#### Secondary endpoints.

postoperative pain at H12: defined as abdominal and/or interscapular pain measured by a Visual Analog Scale (VAS) as following: 0 no pain, 10 worst possible painPostoperative pain at H24: defined as abdominal and/or interscapular pain measured by a Visual Analog Scale (VAS) as following: 0 no pain, 10 worst possible painvomiting: Assessed by: Postoperative Nausea and vomiting (PONV) score defined as follow: 0 no PONV, 1 moderate nausea, 2 moderate vomiting, 3 uncontrollable nausea and/or vomitingConversion rate to open procedureOperative timemorbidity: defined by any surgical complications assessed within 30 days postoperativelypostoperative length of stay

All data will be recorded on a dedicated data collection form (attached S4 File). Patient data will then be analyzed in an anonymized SPSS file.

### Statistical methods

#### Sample size and power.

Using the VAS scale, the mean value of abdominal pain after laparoscopic cholecystectomy with a pressure of 14 mm Hg is estimated in the literature at **4.1 + /-1.8** (H6) [9]. We hypothesize that patients in the low-pressure group will experience significantly lower postoperative pain compared to those in the standard-pressure group (14 mm Hg), with no increase in postoperative morbidity. The difference of means (Δ) is estimated to “01”. For a power level of 90%, a significance level of 5% and a two-way comparison between the two arms of the study, 70 patients/group are needed, i.e., 140 in all. Sample size was overestimated by 20% as per loss of follow-up and/or data discrepancies expectation. An overall sample size of 170 subjects will be enrolled in the study, divided into 85 experimental group vs. 85 placebo group [10]. Allocated study subjects were randomly assigned by, using simple 1:1 non-stratified sequence and a block size of 4.

#### Statistical analysis.

All statistical analyses will be conducted in the intention-to-treat population at a two-sided 5% alpha risk. For each group and at each assessment time, categorical variables will be summarized as numbers and percentages, and continuous variables will be expressed as number, mean, and standard deviation (SD). Quantitative variables with skewed distribution will be presented in terms of median and interquartile range (IQR) (25th-75th percentile).

### Primary endpoint

The primary endpoint is the postoperative pain at 06 hours, assessed by VAS will be compared by Student t test or non-parametric test U of Mann and Whitney when appropriate.

### Secondary endpoints

**Change of VAS over time:** To evaluate the temporal evolution of VAS (at H6, H12 and H24), analysis of variance (ANOVA) with Bonferroni adjustment will be performed. This statistical approach is particularly suited to repeated measures data.Nausea and vomiting: Changes from baseline (H0) to the final time point (H4) will be analyzed within groups using paired ANOVA tests. Between-group comparisons of these changes will be performed using independent ANOVA tests.Duration of hospital stay: the mean hospital stays in each group (control vs intervention) will be compared using t-tests or non-parametric test U of Mann and Whitney when appropriate.Operative time: the mean operative time in each group (control vs intervention) will be compared using t-tests or non-parametric test U of Mann and Whitney when appropriate.Conversion rate: the frequency of conversion rate in each group will be compared by chi²test or fisher exact test when appropriate.30-day morbidity: the frequencies of each postoperative complication in each group will be compared by chi²test or fisher exact test when appropriate.

The statistical analysis will be conducted using SPSS version 26. Analyses will be performed by an independent investigator (CD in the authors’ list) blinded to treatment allocation, ensuring unbiased interpretation of the data.

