### Data collection

#### Baseline assessment (at admission).

Prior to group allocation, each participant’s sociodemographic data (such as age, gender, Body Mass index), baseline characteristics including comorbidities, American Society of Anesthesiologist (ASA) score, preoperative clinical examination, preoperative biological tests, preoperative ultrasound data, and surgical exploration data after trocar placement will be recorded.

Following this assessment, participants will be randomized into one of two study groups.

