#### Postoperative assessment.

The postoperative pain at 6th, 12th, 24th hours, the presence of nausea and/or vomiting, the consumption of painkillers, the duration of hospital stay, the presence of eventual complications within 30 days were recorded.

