#### Data analysis framework.

All analyses will follow the intention-to-treat principle. The primary outcome (VAS pain score at 6 hours) will be compared between groups using an independent t-test or a Mann–Whitney U test if non-normal. An adjusted analysis using ANOVA will be performed with age, sex, BMI, ASA class, and operative time as covariates. Repeated measures of pain (6, 12, and 24 hours) will be analyzed using analysis of variance (ANOVA) with Bonferroni adjustment. Categorical variables, including postoperative nausea and vomiting and complications, will be compared using χ² or Fisher’s exact tests. Continuous secondary outcomes will be analyzed using t-tests or appropriate non-parametric methods. Missing data will be addressed using multiple imputation (fully conditional specification with predictive mean matching), with sensitivity analyses including complete-case and per-protocol analyses. All tests will be two-sided with a significance level of 0.05. Statistical analyses will be performed using SPSS version 26.

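### Nausea and vomiting is given two incompatible analyses, one of them a change between time points (H0 and H4) that the text describes nowhere else

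*Protocol article*

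**What the plan says.** Five places in the protocol article bear on this endpoint.

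- **Secondary endpoints, under Study endpoints (definition).** Postoperative nausea and vomiting (PONV) is a score beginning "0 no PONV, 1 moderate nausea, 2 moderate vomiting", with a top level, 3, for symptoms that cannot be controlled. No time or window is attached.
- **Baseline assessment.** Besides sociodemographic data, comorbidities and ASA score, the list covers "preoperative clinical examination, preoperative biological tests, preoperative ultrasound data, and surgical exploration data after trocar placement will be recorded". It names no nausea score.
- **Postoperative assessment.** The record includes "The postoperative pain at 6th, 12th, 24th hours, the presence of nausea and/or vomiting, the consumption of painkillers". The hours belong to pain. Nausea and vomiting is recorded as present or not, without a time.
- **Secondary endpoints, under Statistical methods (analysis).** Within groups: "Changes from baseline (H0) to the final time point (H4) will be analyzed within groups using paired ANOVA tests". Between groups: "Between-group comparisons of these changes will be performed using independent ANOVA tests".
- **Data analysis framework.** "Categorical variables, including postoperative nausea and vomiting and complications, will be compared using χ² or Fisher’s exact tests".

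**The concern.** The current text prescribes two analyses of one named secondary outcome. They target different quantities, and neither is designated as main or supportive. The choice therefore stays open until the data are seen.

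The more detailed of the two is also a poor fit. It needs a baseline and a four-hour value that the text does not otherwise describe. It treats a postoperative event score as if it had a useful preoperative starting value. It includes tests within each arm, which say nothing about the effect of insufflation pressure. It also averages an ordered four-level score as if the steps were equal.

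At stake is how the trial reports one of its tolerability outcomes. A reader of the results could not tell which analysis had been planned.

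**Working it through.** The plan gives no figure for nausea and vomiting, since the sample size was derived for pain at H6 alone. There is nothing to reproduce numerically, so the check sets the sections side by side.

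**1. What each analysis estimates**

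| Source | Data needed | Quantity compared |
|---|---|---|
| Secondary endpoints (analysis), within groups | Score at H0 and H4 | Mean change in one arm against zero |
| Secondary endpoints (analysis), between groups | Score at H0 and H4 | Difference between arms in mean change |
| Data analysis framework, if the 0–3 score is used | One score per patient | Distribution over four categories, 2 × 4 table, (2−1)(4−1) = 3 degrees of freedom |
| Data analysis framework, if presence is used | Yes or no per patient | Proportion with any symptom, 2 × 2 table, (2−1)(2−1) = 1 degree of freedom |

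A difference in mean change and a comparison of proportions or categories are not two forms of one test. The categorical route is itself open between two tables, because the endpoint is defined as a score but described as presence at collection.

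**2. Whether the time points fit**

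H0 and H4 occur only in the one analysis sentence. The only postoperative hours stated elsewhere are 6, 12 and 24, and these are for pain. H4 is called the final time point, yet in-hospital pain assessment continues to H24. The baseline list contains no nausea score from which an H0 value could come.

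**3. What the change score reduces to**

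Write the change as D = Y(H4) − Y(H0). Assume Y(H0) = 0 for nearly everyone, which is plausible for elective, uncomplicated cases but is not stated in the document. Then D = Y(H4), and:

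- the paired within-group test asks whether the mean of Y(H4) exceeds zero, that is, whether any nausea or vomiting follows surgery;
- the between-group ANOVA compares mean postoperative scores, so the baseline adds nothing.

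Only the second addresses the trial's question.

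**4. What averaging the score assumes**

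The levels run in order from none, through nausea and vomiting, to uncontrollable symptoms. A mean gives the step from 0 to 1 the same weight as the step from 2 to 3. As an illustration, three patients scoring 1, 1, 1 have mean (1+1+1)/3 = 1, and three scoring 0, 0, 3 have mean (0+0+3)/3 = 1. ANOVA sees no difference in mean between these two clinical pictures. For hospital stay and operative time the same section allows a Mann–Whitney alternative; for this score it allows none.

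**The case against.** The strongest defence is that a usable analysis is already in the document. The chi-square or Fisher comparison is a legitimate between-arm test, needs no baseline, and can be run on presence or on the score. The ANOVA sentence is also followed at once by a between-group comparison, and if baseline scores are zero that comparison is simply one of mean postoperative scores: imperfect for an ordered scale, but not invalid merely because it uses change. All of this stands. It limits the severity but does not remove the contradiction, because nothing says which analysis governs. An unseen analysis plan might choose between them, but the published text would still need correcting.

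A reader might infer more than the document supports:

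- **That no H0 or H4 assessment exists.** The schedule figure and the data collection form are not shown. One can say only that none is described in the text.
- **That stopping at H4 discards 20 of 24 hours, (24−4)/24 = 83%.** This borrows the pain schedule. No 24-hour window is stated for PONV, and H4 could be a slip for H24, which cannot be settled from the text.
- **That within-arm tests would mislead up to half the time when the arms do not differ.** The chance that exactly one of two independent tests with power p is significant is 2p(1−p), which peaks at 0.50 when p = 0.5. Nothing in the document supports that p. At p = 0.99 it is 2 × 0.99 × 0.01, about 2%. A direct between-group comparison is planned as well.
- **That the endpoint cannot be analysed, or that the score is unordered.** The categorical test can be run, and the levels are plainly ordered. The fault is the assumption of equal spacing.

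**Conclusion.** The point holds as a contradiction in the current text together with one ill-fitting analysis rule. The contradiction and the scale problem can be seen directly in the document and would remain even if the schedule figure or the form listed H0 and H4. The statement about missing assessments is limited to the text shown. The remark that change reduces to the postoperative score rests on baseline scores being close to zero, which is an assumption.

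No defensible number can be put on the consequence. It affects one secondary endpoint and leaves the primary comparison of pain at H6, the sample size and the main conclusion alone. It should be fixed, but it is not a flaw that threatens the trial.

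**What to change.** 1. In the secondary-endpoint analysis, delete the H0–H4 change analysis of nausea and vomiting, including the within-group tests.
2. State the time or window over which PONV is actually recorded, and whether the 0–3 score or only presence is captured. The sponsor must take this from the schedule and data form.
3. Specify one between-arm comparison. If the score is recorded, use an ordinal method: Mann–Whitney with allowance for ties, or a proportional-odds model. If only presence is recorded, use chi-square or Fisher's exact test and report the risk difference in any PONV with a 95% confidence interval.
4. Make the endpoint definition, the Postoperative assessment section, the secondary-endpoint analysis and the Data analysis framework agree.

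The cost is a wording change if the sponsor describes what is already collected and chooses the matching test. Wanting the score where only presence is captured would mean changing data collection, which the second option in step 3 avoids. The Trial status section puts analysis after follow-up ends, so the correction can be dated and filed before outcome data are examined by arm.

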## Abstract

**Background:**

Laparoscopic cholecystectomy is the gold standard for treating symptomatic gallstone disease. Pneumoperitoneum is essential for adequate visualization during the procedure and is typically maintained at a standard pressure of 12–14 mmHg. However, high insufflation pressure may contribute to increased postoperative pain. This study aims to assess whether low-pressure pneumoperitoneum (8 mmHg) reduces postoperative pain compared to standard pressure (14 mmHg), without compromising operative safety or efficacy. We hypothesize that low pressure pneumoperitoneum at 8 mmHg reduces postoperative pain, without increasing operation time or postoperative morbidity.

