### Hypothesis

The low pressure pneumoperitomenum at 8 mmHg reduces the postoperative pain, at postoperative 6th hour assessment, in patients undergoing laparoscopic cholecystectomy, compared to pneumoperitoneum at 14 mmHg.

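### No increase in operation time or morbidity is hypothesised, but only two-sided difference tests are planned for these secondary endpoints, and they cannot support that claim

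*Protocol article*

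**What the plan says.** The protocol article states its hypothesis in more than one form.

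- **Abstract (Background) and Discussion:** low pressure "reduces postoperative pain, without increasing operation time or postoperative morbidity".
- **Sample size and power:** the expected pain benefit is paired with a morbidity statement, "with no increase in postoperative morbidity". Operation time is not mentioned there.
- **Aim and Hypothesis:** pain only. The Hypothesis section says that low pressure "reduces the postoperative pain, at postoperative 6th hour assessment", and neither section mentions operation time or morbidity.

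The planned analyses are in the Secondary endpoints part of the statistical methods. For operation time, "the mean operative time in each group (control vs intervention) will be compared using t-tests", with Mann-Whitney as the alternative. For 30-day morbidity, "the frequencies of each postoperative complication in each group will be compared by chi²test or fisher exact test when appropriate". The Data analysis framework adds: "All tests will be two-sided with a significance level of 0.05".

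The sample size is set for pain at 6 hours: "For a power level of 90%, a significance level of 5% and a two-way comparison between the two arms of the study". The article gives no margin, confidence-interval criterion or power for operation time or morbidity, and no assumed SD or complication rate for either.

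**The concern.** That a treatment does not increase something is a claim about how large an increase the data rule out. A two-sided difference test answers another question. A significant result can show harm, but a non-significant one is compatible both with no harm and with harm the trial was too small to see. The smaller and noisier the data, the more likely the non-significant result.

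The article names no other criterion for this part of the hypothesis, so the planned tests are the only evidence on which it could rest. The case for adopting low pressure depends on a pain benefit that carries no operative or safety penalty. If the second element rests on absence of significance, that conclusion is unsupported even if the pain result is sound.

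**Working it through.** **1. The plan's own figure.** Inputs from Sample size and power: SD 1.8, difference 1 point, two-sided 5%, power 90%.

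n per arm = 2 × 1.8² × (1.960 + 1.282)² / 1² = 68.1, rounded up to 69. The t-based calculation gives 69.06, rounded up to 70. The stated 70 per group reproduces. Inflation: 140 × 1.20 = 168, close to the 170 enrolled (85 per arm). Only pain at 6 hours enters this calculation.

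**2. Morbidity.** The article gives no complication rate, so control rates of 2%, 5% and 10% are assumed. Any complication is taken as one composite, following the endpoint definition under Study endpoints. Power to detect a true doubling comes from summing exact binomial probabilities over all tables significant at two-sided 0.05:

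| True rates (14 v 8 mmHg) | Power, 85 per arm: Fisher / chi-square | Power, 70 per arm: Fisher / chi-square |
|---|---|---|
| 2% v 4% | 3% / 10% | 2% / 9% |
| 5% v 10% | 16% / 22% | 11% / 20% |
| 10% v 20% | 37% / 45% | 30% / 38% |

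Seventy per arm is the number the plan counts on after losses. The plan tests complications one by one, so each test would rest on fewer events than the composite and have less power for a doubling.

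Precision when the true rates are equal: half-width = 1.96 × √(2p(1−p)/85) = 4.2, 6.6 and 9.0 percentage points at p = 2%, 5% and 10%.

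Two illustrations with 85 per arm (Newcombe intervals, 8 minus 14 mmHg):

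- 4 events in each arm: the upper 95% limit is still +7.4 points.
- 4 v 11 events (4.7% v 12.9%): Fisher p = 0.10, 95% CI −0.5 to +17.5 points. A near-tripling would be non-significant.

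**3. Operation time.** The article gives no SD, so 15, 20 and 30 minutes are assumed. Half-width = 1.96 × SD × √(2/85) = 0.30 × SD.

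| Assumed SD | 95% CI half-width | Power to detect a true 5-min increase | Chance of missing it |
|---|---|---|---|
| 15 min | 4.5 min | 58% | 42% |
| 20 min | 6.0 min | 37% | 63% |
| 30 min | 9.0 min | 19% | 81% |

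A just non-significant result has an observed difference near 0.30 SD and an upper limit near 0.60 SD: about 9, 12 or 18 minutes.

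With a criterion the same data could say more. Take an illustrative 10-minute margin and no true difference. The probability that the upper 95% limit falls below the margin is then about 99%, 90% or 58% at SD 15, 20 or 30. The 10 minutes comes from no document and is not a recommendation.

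**4. Could 85 per arm support a morbidity claim?** Take an illustrative 5-point margin, equal true rates, one-sided 0.025 and 80% power. The need is 124 per arm at 2%, 299 at 5% and 566 at 10%. At these rates it could not.

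**The case against.** The best defence is that the sections headed Aim and Hypothesis name pain only, that operation time and morbidity are secondary, and that powering a trial on its primary endpoint is ordinary practice. All of that is true. It rules out calling the no-increase statement half of the formal hypothesis, and it lowers the severity. It does not remove the mismatch, because the statement is worded as a hypothesis in the abstract and the Discussion and, for morbidity, in the sample-size section.

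A reader might infer that the plan contains a rule under which p > 0.05 will be declared to mean no increase. It does not. That reading is an inference, invited by the lack of any other criterion, and the abstract's conclusion is conditional on the results. A reader might also infer that the trial cannot exclude a clear increase in either endpoint. For operation time the article does not support this: with an SD of 20 minutes or less and a difference near zero, the confidence interval could exclude about 10 minutes.

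The morbidity powers describe a composite, whereas the plan compares each complication separately, so they are not the power of the analysis as written. Separate tests have sparser counts, so this does not help the plan.

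Finally, confidence intervals are often left to an analysis plan, which is not at hand. But the article already fixes the tests for these endpoints, and those tests cannot answer the hypothesis it states.

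**Conclusion.** The point holds and should be fixed, though it is not critical. The article hypothesises no increase in operation time and morbidity, and plans only tests that cannot establish it.

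For morbidity the weakness is present at every assumed control rate from 2% to 10%: a true doubling is more likely to be missed than found, with power between 3% and 45% at 85 per arm and lower at 70. For operation time it is conditional on an SD the article does not give, with a 95% CI half-width from 4.5 to 9.0 minutes across SDs of 15 to 30. All these sizes rest on assumed rates and SDs; the mismatch between hypothesis and test does not.

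The primary pain analysis and its sample size are unaffected.

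**What to change.** 1. In Secondary endpoints and the Data analysis framework, report the mean difference in operation time and the risk difference for any 30-day surgical complication (the article's own morbidity definition), each as 8 minus 14 mmHg with a 95% CI. State that p > 0.05 will not be reported as no increase.
2. Remove no increase in morbidity as a hypothesis from the abstract, the sample-size section and the Discussion, in line with the Hypothesis section. Treat morbidity as a descriptive safety outcome and state the largest increase the data do not exclude.
3. For operation time, choose one of two routes. Either treat it the same way and drop the wording, or claim no increase only if the upper 95% limit lies below a margin that the sponsor justifies and fixes before unblinding. Recruitment is already under way, so the date on which any margin is set should be recorded.

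The cost is changed wording and two confidence intervals, with no new data or patients. The downside is a more modest safety conclusion.

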**Methods:**

This is a single-center, randomized, controlled, double-blind trial. Consecutive Adult patients scheduled for elective laparoscopic cholecystectomy will be randomized in a 1:1 ratio to receive either low-pressure (8 mmHg) or standard-pressure (14 mmHg) pneumoperitoneum. The primary outcome is postoperative abdominal pain assessed using the Visual Analog Scale (VAS) at 6 hours after surgery. Secondary outcomes include VAS pain scores at 12 and 24 hours, postoperative nausea and/or vomiting, postoperative hospital stay and postoperative 30-day morbidity. The enrollment of patients will be done between November 12, 2024 to December 31, 2025.

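### 30-day morbidity is defined as any surgical complication, but its stated analysis compares each complication separately, so no single morbidity estimate is specified for the no-increase hypothesis

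*Protocol article*

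**What the plan says.** All references are to the protocol article.

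- **Endpoint.** Study endpoints, Secondary endpoints: morbidity is "defined by any surgical complications assessed within 30 days" after surgery. The Abstract (Methods) lists it as one outcome, "postoperative hospital stay and postoperative 30-day morbidity".
- **Morbidity-specific analysis.** Statistical methods, Secondary endpoints: under 30-day morbidity, "the frequencies of each postoperative complication in each group will be compared by" chi-square or Fisher's exact test.
- **General analysis.** Data analysis framework: "Categorical variables, including postoperative nausea and vomiting and complications, will be compared using" chi-square or Fisher's exact tests. It also says "All tests will be two-sided with a significance level of 0.05".
- **Hypothesis.** The Abstract (Background) and the Discussion expect less pain "without increasing operation time or postoperative morbidity". Sample size and power repeats the idea: "with no increase in postoperative morbidity".

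**The concern.** The endpoint reads as one outcome, naturally a yes or no per patient. The analysis written for it is a set of tests, one per type of complication. The article does state an analysis here, so this is not simply detail left to a fuller document: the stated analysis does not match the stated endpoint.

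Morbidity is half of the trial's argument, which is less pain at no cost in complications. A reader of the results will want one number: how many more, or fewer, patients had a complication at 8 mmHg, and with what uncertainty. A column of p-values on rare events does not supply it, and a column of non-significant ones could be taken as support for no increase when it says little.

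**Working it through.** **1. Endpoint against analysis.** The endpoint covers any complication, the specific analysis takes each complication, and the general sentence speaks of complications without giving the unit. No sentence specifies a comparison of patients with at least one complication.

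**2. The plan's own figures.** None is given for morbidity: no rate, margin or power. The sample size is for pain at 6 hours (difference 1, SD 1.8, two-sided 5%, power 90%):

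- n per arm = 2 × 1.8² × (1.960 + 1.282)² / 1² = 68.1, so 69. The t-based figure is 69.06, so 70, as stated.
- Allowance of 20%: 140 × 1.2 = 168, or 140 / 0.8 = 175. The stated 170 (85 per arm) lies between.

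The pain calculation reproduces. It says nothing about complications.

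**3. What one complication type needs.** With 85 per arm and no events in one arm, the two-sided Fisher p-value for k events in the other is 2 × C(85,k) / C(170,k).

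- k = 5: p = 0.0588
- k = 6: p = 0.0285

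So 6 v 0 is the smallest significant split.

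**4. Separate tests against one composite test.** The rates and the number of types are assumptions, because the article gives none. Take six independent types, 85 per arm and exact two-sided Fisher at 0.05. If s is the power for one type, the chance that at least one of six equal tests is significant is 1 − (1 − s)⁶. The composite rate is 1 − (1 − p)⁶.

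| Assumed harm | Any complication, by arm | At least one separate test | Composite test |
|---|---|---|---|
| All six types, 1% v 3% | 5.9% v 16.7% | 11% (s = 2.0%) | 55% |
| All six types, 2% v 4% | 11.4% v 21.7% | 17% (s = 3.0%) | 36% |
| All six types, 2% v 6% | 11.4% v 31.0% | 55% (s = 12.5%) | 85% |
| One type 1% v 10%, five at 1% | 5.9% v 14.4% | 66% | 38% |
| One type 2% v 10%, five at 2% | 11.4% v 18.7% | 49% | 20% |

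In the last two rows the raised type supplies nearly all the power of the separate tests, and the composite rate at low pressure is 1 − 0.99⁵ × 0.90 = 14.4% or 1 − 0.98⁵ × 0.90 = 18.7%.

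A different structure, with 3 to 5 mutually exclusive and equally frequent types, agrees for spread harm. At 5% v 15% overall, the composite has 51.5% power, against 23.3% (3 types) to 9.5% (5 types) for at least one separate test.

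**5. How far the composite goes alone.** Exact Fisher power at 85 per arm is 7% for 3% v 6%, 16% for 5% v 10%, 37% for 10% v 20% and 52% for 5% v 15%.

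**6. Why the interval matters.** Suppose 5 of 85 patients have a complication at 14 mmHg and 8 of 85 at 8 mmHg (invented counts). The difference is 0.0941 − 0.0588 = 0.0353. The standard error is √(0.0588 × 0.9412 / 85 + 0.0941 × 0.9059 / 85) = 0.0407. The 95% CI is 0.0353 ± 1.96 × 0.0407, that is −4.4 to +11.5 percentage points. Fisher gives p = 0.57, yet an increase of 11 points is not excluded.

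**The case against.** **The definition can be read otherwise.** The endpoint sentence uses a plural and does not say at least one per patient. It may only set the scope, with the by-type comparison as its breakdown. This has some force, but the Abstract lists morbidity as a single outcome, and on either reading no overall comparison is specified.

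**A reader might infer that the composite will never be compared.** The documents do not support that. The general sentence in the Data analysis framework could cover an any-complication variable, and nothing rules one out. The comparison is unspecified, not excluded.

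**A reader might infer that most of the power to see harm is lost.** That depends on assumed rates and on the pattern of harm. With 2% v 6% in every type, the loss is from 85% to 55%, about a third. With harm in one type, the ranking reverses. The documents give no basis for choosing between these patterns.

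**A reader might infer that many tests invite a chance finding.** At the assumed rates this is weak. With no true difference, at least one of six Fisher tests is significant in 0.1% of trials (1% per type) or 1.7% (2% per type).

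**The change cannot establish no increase.** This is right, as step 5 of the working shows. It gives the hypothesis an estimate and an interval, and nothing more.

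**Conclusion.** The point holds as a mismatch between endpoint and analysis, and that needs no assumed rate. The endpoint is any surgical complication, the only analysis specific to it is complication by complication, and the general sentence does not settle the unit. As written, the plan specifies no single morbidity estimate for the hypothesis of no increase.

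The size of the consequence does depend on assumptions. For harm spread over six types, separate tests detect it less often than the composite (11% v 55%, 17% v 36% and 55% v 85%). For harm in one type they detect it more often (66% v 38% and 49% v 20%). The case for the composite is therefore that it answers the stated question, not that it is always more powerful.

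Severity is minor to moderate. This is a secondary endpoint, and the primary analysis and sample size are untouched.

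**What to change.** In Statistical methods, Secondary endpoints, replace the 30-day morbidity sentence with wording such as:

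> 30-day morbidity is the proportion of patients with at least one surgical complication within 30 days. It is compared between arms as a risk difference with 95% confidence interval, with a chi-square or Fisher's exact p-value alongside. Individual complication types are also tabulated by arm as supporting information.

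Add that the trial is not sized for morbidity, so a non-significant result is interpreted through the confidence interval and not as proof of no increase.

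The cost is a short text change and one extra analysis, using complications already recorded to 30 days. It should be made before unblinded analysis. The drawback is that a composite can dilute a harm confined to one type, which is why the by-type table stays. Whether to attach p-values to that table is a matter of preference.
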